## **2.8. Study Area**

The trial will be carried out in rural villages in Muleba district (1° 45'N, 31° 40'E), in Kagera region of north-west Tanzania (fig. 1). Muleba District covers an area of 10,739 km^2, of which Lake Victoria is 62%. Most of the district lies at 1200-1500m above sea level. Administratively the district has 31 wards, 134 villages and a population of 425,172 people (URT, 2003) with 85,035 (20%) children <5 years old. The district has 36 health facilities comprising 3 hospitals (Rubya, Kagondo and Ndolage), 4 health centres and 29 dispensaries. Parasitaemia and anemia prevalence ranges widely between villages. *An. funestus* is the predominant vector in many villages within the district, representing 58-66% of the total catch (NIMR, unpublished data).

The district was chosen as a launch site for PMI-funded spray operations in 2007. In 2009 PMI supported three rounds of IRS in Muleba district, achieving over 90% coverage (fig. 2).

[figure not shown]

One of the host country partners, NIMR, has a significant presence in Muleba district and has been directly involved with monitoring the PMI IRS spray programme through follow-up entomological

surveys and the monitoring of mosquito resistance in the district. It is hoped to integrate their involvement within the Project.

LSHTM and KCMC also have a long term presence there at a research station in Mwanza, a centre for research on STIs and HIV. Through these offices the NIMR, LSHTM and KCMC malaria groups can readily expand its geographic range to Kagera region.

## **2.9. Co-ordination Committees**

The research project involves several stakeholders and interested parties commitment of which is essential to success. The Project is working closely with RTI to co-ordinate spraying of study villages, NMCP which is responsible for all malaria control activities in Tanzania, MEDA/World Vision/PSI who are involved in LLIN distribution. Regular communication is necessary with the district medical representatives to link up with dispensaries, enable timely and adequate provision of RDTs and ACTs, and working with nurses and clinicians. Two co-ordination committees will be established. The first will include senior representatives of WHO, NMCP, RTI and PMI/USAID as a way of informing on project progress in Dar es Salaam. The second committee will be at the regional level involving the district medical officer, malaria focal person, RTI representatives.

## **3. Research activities under the work plan**

### **3.1. Mapping of study area**

During initial visits we identified and geo-located 75 villages within the district that were accessible and within a travelling time from PAMVERC office in Muleba town of less than 45 min. The study area has since been extended to cover a total of 113 villages across 29 wards. These villages lie in an area of approximately 2000km^2 extending 70km North to South and 68km East to West, at an elevation ranging between 1110 to 1640m above sea level. The total population of the study area is around 68,000 houses.

Every building of each hamlet mapped using a Global Positioning System handled units (GPS) (Garmin Legend e-trex) and ExpertGPS v3.8 (TopoGrafix) software. Boundary of each hamlet, health facilities and other landmark are also geo-located (figure 5).

### **3.2. Cluster identification**

With the maps it becomes possible to identify clusters to use in the cross sectional prevalence survey (figure 5 and 6). Each cluster will be comprised of at least one village, because the village is the smallest unit we can refer to when directing the different vector control measures (IRS and LLIN distribution) during our intervention year. By dragging concentric circles over the maps we can identify suitable clusters of one or more villages. Each cluster includes:

- a. A core sampling area of approximately 1 km radius including a minimum 200 household where the cross sectional surveys and entomological monitoring are conducted
- b. A buffer zone of at least 1 km surrounding the core sampling area, where hamlets will receive the same intervention as the survey area.

[figure not shown]

**Figure 1.** Hamlet distribution (■ = village centre) in the study area. Each shape represents a Hamlet. Clusters are identified with a same colour and the plain shapes show the core sampling areas within the cluster where surveys are going to take place. In the example circled in red the cluster is formed by 9 hamlets, 2 are part of the core sampling area and the 7 other are in the buffer zone.

[figure not shown]

Figure 6. Detailed map of one cluster. Small black dot represent the houses.

### 3.3. Cross-Sectional Surveys

#### 3.3.1. Overview

There will be four cross-sectional surveys during the study period;

- Pilot cross sectional survey– February - March 2011
- Baseline cross sectional survey– June 2011

Intervention: Withdrawal of spraying in one arm September 2011

- Post Intervention Survey A– February - March 2012, 5 months after the intervention
- Post Intervention Survey B– June 2012, 8 months after the intervention

Each survey will include two components; 1) a household component and 2) a parasitological component. The household component will be conducted in 100 houses selected at random from the core sampling area (figure 7). A questionnaire will be administered to obtain information on possible

risk factors for malaria and a maximum of two children from eligible household will be selected. Children will be sent to a central point the following day for the parasitological testing.

[figure not shown]

**Figure 7:** Detailed map of the survey area of one cluster. Blue flag represent the houses that have been selected for the survey and need to be visited. Green dot indicate the other houses.

### 3.3.2. Pilot Cross sectional survey

#### Objectives of the Pilot

1. To estimate the malaria prevalence rate in each of the 51 clusters,
2. To determine the cluster sample size for the main study
3. To select the clusters with the highest prevalence rates for inclusion into the main study
4. To pilot the process and tools to find any problems
5. Determine the age distribution of malaria parasite prevalence and guide the age ranges to be included in the following surveys

#### Household component

One hundred households are randomly selected from the core sampling area of every cluster. In each house a maximum of two children between 6 months and 14 years will be selected. This will yield approximately 100 children allowing for refusals and non-response. A total of 5000 children are expected to be surveyed. Paper questionnaires are used and are double entered by two data-entry clerks into an access database.

#### Parasitological component

All selected children have their temperature taken, and are tested for malaria parasites using RDTs, thick and thin blood smears. When RDT is positive free treatment for malaria will be provided. Children with severe malaria or any other disease that can't be treated by the team will be referred to the nearest health facilities.

The slides will be fixed, stained and checked for quality in Muleba by a laboratory technician. Slides are double read, blind by two experienced microscopists. Slides are declared negative after reading 200 fields. If positive, parasite species are reported (including mixed infections) and are counted against 200 white blood cells. Gametocytes are recorded for *Plasmodium falciparum*.

#### Selecting the clusters for baseline and post interventions surveys

The selection of the determined number of clusters for the main study will be based on the following criteria determined from the pilot cross-sectional survey:

1. Clusters with the highest estimated malaria prevalence will be included.
2. Exclusion of all clusters that include any areas that have not been sprayed in the last spray round.

Allocation to the two arms will be at random, stratified by malaria prevalence and population size as determined by the pilot study.

### 3.3.3. Baseline and post intervention surveys

These surveys will follow the same process than the pilot survey. However the questionnaire will be more detailed and additional tests (haemoglobin, serology, PRC) included in the parasitological component. The age distribution of the individuals to be included in these surveys will be based on the finding of the pilot study result.

#### Objectives of the baseline survey

1. To determine if the two arms are similar in terms of malaria indicators
2. To determine the coverage of LLINs and evaluate the universal coverage campaign
3. To evaluate the usage and perception of existing LLIN in baseline year
4. To evaluate perception of IRS in baseline year
5. To determine the risk factors for malaria
6. To determine the effect of LLIN integrity on malaria prevalence

#### Objectives of the post-intervention surveys

*Compare the two study arms in terms of:*

1. Malaria prevalence
2. Mean haemoglobin (g/dL) in children under 5 years old
3. Sero-conversion rates

4. Entomological Inoculation Rate (EIR) for each mosquito vector species.
5. Relative population density for each mosquito vector species

*Evaluate:*

6. Usage and perception of LLIN in an environment of reduced IRS.
7. Coverage and perception of IRS and the withdrawal of IRS
8. To determine the effect of LLIN integrity on malaria prevalence

Household Survey – modifications from the pilot

The survey will include additional information on, educational status and occupation, social economic status (SES) and house structure. Additional question on nets will be elaborate to evaluate the LLIN distribution campaign process of March 2011, source of net and net usage and reason of non usage. The IRS section will also include in-depth information on coverage and perception and acceptance of IRS.

It is planned to use a Personal Digital Assistant (PDA) for the household questionnaire during baseline and post interventions cross sectional surveys.

Parasitological Survey– modifications from the pilot

Additional data and test will be performed:

- History of fever in the last 48 hours will be recorded
- Only individuals with current or history of fever in the last 48 hours will be tested for malaria with an RDT.
- **PCR.** A blood spot on filter paper will be collected for PCR determination of sub-patent infections since prevalence is low. This is to be done for all individuals. The presence of parasite may have been much reduced as a result of the previous IRS campaigns.
- **Force of infection as determined using serology:** A blood spot on filter paper will be collected for serological estimation of antibodies to malaria. Which individuals will be sampled for serology will be determined by the pilot and through discussion with serology specialists. As vector control has been ongoing since 2007 serology will show us the change in the force of infection over time since IRS intervention began. The purpose is to determine whether malaria prevalence fell around the time IRS spraying began.
- **Prevalence of anaemia:** Haemoglobin will be measured using Hemocue and the prevalence of anaemia (<8g Hb/dL) will be calculated. Body weight, height and upper mid-arm circumference will be measured to allow adjustment for possible malnutrition. Iron supplementation will be given to any child with anaemia (Hb<8 g/dL).

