|                                                                                                                                                   |                                                               | - House structural data                                                                                                                                                                                                                                                                                                                                               |                                                                                 |
|                                                                                                                                                   | Detection of Pf infection by RDTs, bloodslides, PCR    | 
 
• 3000 children surveyed
 
• XXXX adult surveyed
 
• 3000 RDTs taken and read
 
• 3000 slides stained and double read
 
• PCR detection of Pf from bloodspots
 
• Pf % prevalence by age group and diagnostic technique
 
                                            | 
June-July 2011
 
“
 
“
 
September 2011
 
“
 
“
 |
|                                                                                                                                                   | Sero-prevalence (bloodspot ELISA)                             | 
 
• Impact of IRS on sero-conversion rates by age group and spray history
 
                                                                                                                                                                                                                                             | September 2011                                                                  |

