|                                                                                                                     | Detection of Pf infection by RDTs, bloodslides, PCR | 
 
3000 children surveyed
 
3000 RDTs taken and read
 
3000 slides stained and double read
 
PCR detection of Pf from bloodspots
 
Pf % prevalence by age group and diagnostic technique
 
                                                                                                                                                                                                                                                                    | Feb-March 2012
“
End April 2012
“
“ |
|                                                                                                                     | Sero-prevalence (bloodspot ELISA)                          | 
 
Impact of IRS on sero-conversion rates by age group and spray history
 
                                                                                                                                                                                                                                                                                                                                                                                                                              | May 2012                                        |
| Cross-sectional post intervention survey
B
(100 children from ~100households in each of ~30 clusters)  | Questionnaires                                             | 
 
Completion of questionnaire survey in ~7100houses within each of 30 clusters
 
Household census & risk factors data 
 
Socioeconomic data
 
Bednet usage; IRS and other insecticide use
 
 
 
% of children who slept under an ITN/LLIN on the previous night
 
% of households with evidence of IRS in
 
                                                                                                                | April-May 2012                                  |

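### Section 3.3.3 limits the RDT at the trial surveys to recent fever, but the work plan counts one RDT per child; if section 3.3.3 governs, a child with Hb<8 g/dL and no recent fever gets iron but no RDT

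*Protocol*

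**What the plan says.** Section 3.3.3 carries the pilot procedure into the trial surveys: "These surveys will follow the same process than the pilot survey". It then lists changes. One concerns the RDT: "Only individuals with current or history of fever in the last 48 hours will be tested for malaria with an RDT". Another adds a haemoglobin measurement: "Iron supplementation will be given to any child with anaemia (Hb<8 g/dL". No malaria test is attached to that finding.

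In the pilot (section 3.3.2, Parasitological component), every selected child had an RDT and blood smears. The treatment rule there is "When RDT is positive free treatment for malaria will be provided". Children with severe malaria, or with another illness beyond the team's means, are referred to a health facility.

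The work plan (section 4, Stages III and IV) lists, for the baseline survey and for post-intervention surveys A and B, 3000 children, "3000 RDTs taken and read" and "3000 slides stained and double read". The baseline entry alone also has the unfinished line "XXXX adult surveyed".

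**The concern.** Two parts of one protocol give different rules for who is tested. Field teams and RDT procurement need a single rule. The work plan also promises *P. falciparum* prevalence by diagnostic technique, and an RDT prevalence in all children cannot be produced if only those with recent fever are tested.

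The second issue is care. In the pilot every child was tested, so a treatment rule that depended on a positive RDT reached every child. Section 3.3.3 narrows the testing and so narrows the treatment trigger, and nothing is put in its place. The same section adds a measurement that picks out children with Hb<8 g/dL. In a malaria trial with RDTs already at the survey point, such a child would be given iron and, without recent fever, no malaria RDT. Two of the three surveys take place after IRS has been withdrawn in one arm.

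**Working it through.** **1. The work plan count.** Inputs from section 4: 100 children per cluster and about 30 clusters. 100 × 30 = 3000 children, which reproduces the stated figure. RDTs per child = 3000 / 3000 = 1.00.

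**2. The count under section 3.3.3.** RDTs per survey = 3000 × f, where f is the share of children with current or recent fever. The documents do not give f.

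| f (assumed) | RDTs per survey | Children without an RDT |
|---|---|---|
| 5% | 150 | 2850 |
| 20% | 600 | 2400 |
| 50% | 1500 | 1500 |
| 100% | 3000 | 0 |

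The two rules agree only at f = 100%. This is firm for surveys A and B, which list children only. At baseline an unstated number of adults is also listed and section 3.3.3 speaks of individuals, so some of those 3000 RDTs could be for adults.

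**3. The route to treatment if section 3.3.3 governs.** Take a child with Hb<8 g/dL and no fever now or in the last 48 hours.

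- RDT: not done (section 3.3.3).
- Iron: given (section 3.3.3, Prevalence of anaemia).
- Antimalarial treatment: the stated trigger is a positive RDT (section 3.3.2, carried over by section 3.3.3), which cannot occur without a test.
- Referral: covers severe malaria or illness the team cannot treat, so it does not detect an infection that is not clinically evident.
- Slide: taken from every child, but no sentence links a positive slide to treatment.

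**4. Size.** The number of children who are infected, have Hb<8 g/dL and have no recent fever cannot be derived: neither the share with Hb<8 g/dL nor the share of infected children with fever is given. A wider group can only be illustrated. Infected children without recent fever = 3000 × p × (1 − g), where p is a Table 1 prevalence and g is the share of infected children with recent fever, assumed to be 10% to 50%.

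- p = 4%: 120 infected, of whom 60 to 108 would have no RDT.
- p = 8%: 240 infected, of whom 120 to 216 would have no RDT.
- p = 10%: 300 infected, of whom 150 to 270 would have no RDT.

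These are scenarios. The children with Hb<8 g/dL are a subset of unknown size.

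**5. Effect on outcomes.** Slides are planned for all 3000 children and PCR for all individuals, so prevalence by either method does not depend on who has an RDT.

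**The case against.** The strongest reply is that the conflict is a tidying matter. One side of it is a count in a planning table with unfinished entries, and the primary prevalence outcome does not depend on it. The care argument also rests on silence. The protocol says that a positive RDT leads to treatment; it does not say that nothing else can. Section 3.8 has a clinician approving each clinical form, and the staffing list includes nurses and two clinical officers, who may act on their own judgement. If the work plan governs, the gap at the visit disappears.

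Much of this stands. It makes the care issue conditional, and a gap in the stated rules rather than proof that children go untreated. It does not remove the issue: section 3.3.3 states a rule that, followed as written, withholds the RDT from a child with Hb<8 g/dL and no fever, and the presence of a clinician does not supply the test.

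Some stronger readings are tempting, and the documents do not support them.

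- *The Table 1 prevalences cap the number of infected children.* They are planning scenarios. The trial selects the clusters with the highest prevalence, and section 2.8 reports 10-31% in selected villages before IRS.
- *The slide dates show that a child's result would come too late.* They are target deadlines for a batch of 3000 double-read slides and do not show when any one slide is read.
- *Iron must wait for the RDT result.* Nothing in the protocol says that iron given without a malaria result is harmful.

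**Conclusion.** The contradiction is certain at surveys A and B and probable at baseline, where the unstated number of adults blurs the count. Section 3.3.3 is the likelier rule, since it is a deliberate change in the procedural text, but the protocol does not settle this.

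If section 3.3.3 governs, a child with Hb<8 g/dL and no recent fever is given iron, is not tested by RDT, and so cannot meet the only treatment trigger stated. How many children this affects cannot be computed from the documents. A reader might infer that the prevalence comparison is compromised; it is not, because slides and PCR cover everyone. The only loss to the data is an RDT prevalence in all children. The point deserves correction because the rule as written gives worse care than the pilot's and a small change in wording repairs it.

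**What to change.** In section 3.3.3, replace the RDT sentence with wording such as: *An RDT will be done for every individual who has fever now, has had fever in the last 48 hours, or has Hb<8 g/dL; those who test positive will be treated free of charge at the visit, as in the pilot.* Correct the RDT counts for the baseline survey and for surveys A and B in section 4 to the tested subset. If the sponsor intends every child to be tested, delete the fever restriction and keep the counts.

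The cost of the first option is a small number of extra RDTs and ACT doses, limited to those with Hb<8 g/dL and no recent fever. RDTs are already used at these surveys. Universal testing would need more of both.

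How children with a positive slide are followed up is a secondary question for the sponsor and not part of the required change. Tracing them would need field resources. Treatment after survey A could also narrow the arm difference at survey B, which in this trial leans towards non-inferiority. The minimum core is 200 households (section 3.2) and 100 houses are surveyed (section 3.3.1), so the survey can reach 100 / 200 = 50% of the smallest cores. The size of that effect cannot be computed from the documents.

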### 3.4. Incidence

The plans for establishing a new incidence indicator based on passive case detection through government, NGO and faith group health facilities was described in section 2.7. Consensus and new commitment would be required by the Ministry of Health, district health services, PMI, RTI among others. The facilities to include would be those serving the study area catchment clusters. Sufficient RDTs and ACTs need to be made available. That may require repartitioning of government or PMI resources from other districts and it is presently unclear whether there is sufficient budget flexibility to establish the new system. Ideally provision should be made throughout the study periods (baseline and intervention years), but if this is not feasible provision should assigned to the peak malaria seasons

during the two years. To use clinical incidence data as a study outcome requires that the cluster in which each patient lives is known. It is intended that this will be done by issuing identification cards to participating households in each cluster, and asking householders to bring these to the clinic with them, so that this can be noted in the register. This will require the necessary collaboration from clinics in the study area. If this system is not feasible we shall encourage clinics to ask information about the village of residence of all outpatients with suspected malaria (prior to RDT) and analyse the data accordingly.

